### ***Hypothesis, aim and objectives***

Our broad hypothesis is that by improving the knowledge of ED infected patients and by introducing new diagnostic tools, which contribute to the development of rapid and more accurate diagnosis of acute infections, a more appropriate antibiotic therapy can be administered.

The project aims to adapt and evaluate alternative diagnostic tools and working methods that support a prompt and accurate diagnosis of hospitalized patients suspected of an urgent infection – with special focus on pneumonia and acute pyelonephritis.

The research objectives are:

- 1) What is the patient characteristics and course of treatment of the different ED infections?
- 2) What is the diagnostic value of the infection markers PCT, suPAR, and CRP in patients with suspected pneumonia and pyelonephritis?
- 3) What is the diagnostic value of the lung injury markers SP-D, YKL-40, and KL-6 on diagnosing pneumonia
- 4) What is the impact of bedside-US and ULDCT on diagnosing pneumonia ?
- 5) What is the impact of advanced US on diagnosing pyelonephritis?
- 6) What is the impact of bedside-US on diagnosing hydronephrosis?
- 7) What is the impact of POC-PCR analysis of sputum on antibiotic prescriptions?
- 8) What is the impact of POC urinary flow cytometry on diagnosing and excluding bacteraemia?

The goal is to combine the results of all these eight objectives into one novel diagnostic model which the ED physician can apply when patients with suspicion of an infection is admitted.

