### ***Additional POC-PCR analysis of sputum if suspected pneumonia***

A sputum samples will be collected according to standard procedure as soon as possible after recruitment. The sample will be divided into two aliquots; one for routine sputum culturing by the Microbiological Department, and one for additional analysis.

The sample for additional analysis will be randomly assigned to one of two groups with 1:1 allocation:

1. Control: no POC-PCR will be done and no further intervention will be performed.
2. POC-PCR analysis linked to advice from microbiologist: Sputum samples will be analysed by the study assistant and results will be saved in the local microbiological database. The study assistant will tell a study microbiologist to contact the physician upon performing the 4-hour-treatment plan, and discuss optimal antibiotic treatment plan for the patient based on clinical sign and symptoms, chest X-ray, routine blood analyses and results from POC-PCR analysis.

The POC-PCR used in this study is by Biofire FilmArray Pneumonia Panel plus (Biomérieux, Marcy l'Etoile, France), which is a closed automatic system, nested multiplex PCR, that includes all the steps of molecular diagnostics, with running time of about 75 min, including sample preparation and nuclei-acid extraction. The panel includes 15 typical bacterial pathogens, three atypical bacterial pathogens, nine viruses and seven antimicrobial resistance genes. The results for typical colonizing bacteria are reported semi-quantitatively providing estimates to the nearest whole log as genome copies/ml ranging from  $10^4$  to  $10^7$  copies/mL, results from viruses, fungus and atypical bacteria are reported as "detected" or "not detected" and antimicrobial resistance genes are reported qualitatively in the case of simultaneous detection of a compatible pathogen. Testing of specimens using the panel will be conducted in accordance with the manufacturer's instruction (43). Each site will have a pocket laboratory protocol to ensure consistent data collection in quality and safe handling of specimens.

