#### *Effect of POC-PCR on antibiotic prescription*

The antibiotic prescribed in the 4-hour plan, will be collected. The antibiotic type will be classified in four groups; 1) no antibiotic prescription, 2) narrow spectrum antibiotics, 3) broad spectrum antibiotics and 4) broad spectrum antibiotics not targeting pneumonia treatment. The primary outcome is to investigate difference in type of antibiotic prescription in the three randomization groups.

Secondary outcomes include revision of antibiotic treatment at 48 hours, registered adverse events (e.g. length of stay, in-hospital mortality, 30-days mortality and clostridium infections), and agreement between POC-PCR results and results of sputum culture.

To achieve a power of 82% for the main analysis, 200 patients with suspected CAP must be included. Generalized mixed effect models will be adjusted for strong predictors. If the sample size is not sufficient for a generalized mixed effect models the corresponding univariate analysis will be conducted

*Amendment:* Intervention group: sputum samples analysed by POC-PCR. Control group: routine microbiology analysis. It is a superiority randomized trial. Primary outcome is targeted versus non-targeted antibiotic treatment prescribed at four hours after admission. Targeted treatment is defined as narrow spectrum antibiotics directed against CAP, antibiotics directed against a detected respiratory pathogen or no antibiotics (e.g. in the absence of a bacterial pathogen and/or presence of a viral pathogen). Non-targeted treatment is defined as broad spectrum antibiotics not directed against a specific pathogen or antibiotics not directed against CAP. (Appendix VI - Algorithm for antibiotic treatment). The analyses will follow the intention-to-treat principal and a hierarchical mixed effect logistic model will be utilized to analyze the primary outcome to accommodate the hierarchical structure of the random effect, which manifest according to different personnel collecting the samples and geographical variation.

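### The randomised intervention is POC-PCR together with a microbiologist's advice, but objective 7 and the amendment describe it as POC-PCR alone, a more specific claim than the design can support

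*Protocol*

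**What the plan says.** Under Hypothesis, aim and objectives, objective 7 asks: "What is the impact of POC-PCR analysis of sputum on antibiotic prescriptions". The advice is not mentioned there.

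The section Additional POC-PCR analysis of sputum if suspected pneumonia sets up the comparison: "The sample for additional analysis will be randomly assigned to one of two groups with 1:1 allocation". The first arm is "Control: no POC-PCR will be done and no further intervention will be performed". The second is "POC-PCR analysis linked to advice from microbiologist: Sputum samples will be analysed by the study assistant". The advice has a fixed moment: "The study assistant will tell a study microbiologist to contact the physician upon performing the 4-hour-treatment plan". Its content goes beyond the panel, because the microbiologist is to "discuss optimal antibiotic treatment plan for the patient based on clinical sign and symptoms, chest X-ray, routine blood analyses and results from POC-PCR analysis". The Procedure section also ties the POC-PCR analysis to guidance from microbiology.

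The outcome section is headed as the effect of POC-PCR on prescribing. Its amendment defines the arms again, this time as "Intervention group: sputum samples analysed by POC-PCR" against routine microbiology, and again leaves the advice out. It sets the primary outcome as targeted versus non-targeted treatment prescribed four hours after admission.

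**The concern.** The arms differ in two respects, while the objective and the amendment name one. The second is a specialist's discussion of the case with the prescriber, at the time of the prescription that serves as the primary outcome. Three of the four listed inputs to that discussion (symptoms and signs, chest X-ray, routine bloods) are not produced by the panel, and controls receive no study-initiated discussion of such information.

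What is at stake is the conclusion. Read by objective 7 and the amendment, a positive result would be reported as the effect of the PCR panel on prescribing. The protocol also intends to combine the results of all eight objectives into one diagnostic model, so the label would travel with the result.

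**Working it through.** The point rests on no figure in the plan, so the main check is to set the places side by side.

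| Place in the protocol | POC-PCR | Microbiologist's advice |
|---|---|---|
| Objective 7 | named | not named |
| Procedure | named | named |
| POC-PCR section, intervention arm | named | named, with timing and content |
| POC-PCR section, control arm | excluded | excluded (nothing further is done) |
| Outcome section, heading | named | not named |
| Outcome section, amendment | named | not named |

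**Step 1: can the components be separated?** Two arms are defined: both components, or neither. No arm has advice without PCR, or PCR without advice. The outcome section still mentions three randomised groups, but no third group is defined anywhere, so this does not help.

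**Step 2: can the analysis separate them?** The amendment plans an intention-to-treat analysis with a hierarchical mixed logistic model whose random effects reflect collecting personnel and geography. Advice is a function of arm, so within arm it does not vary by design. No covariate or random effect can split the arm coefficient.

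**Step 3: can the advice act on the outcome by itself?** Targeted treatment has three routes: narrow-spectrum treatment for CAP, treatment directed at a detected respiratory pathogen, or no antibiotic. Advice drawn from routine information could plausibly lead to the first or third. The second depends mainly on the panel, since the Background says that sputum culture often reports after discharge or after treatment has ended. So the advice can move part of the outcome without the panel, but not all of it.

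**Step 4: an illustration of scale, on assumptions only.** The plan states 82% power with 200 patients for this comparison, without rates, effect size, alpha or sidedness, so the figure cannot be reproduced. Assume 100 per arm, two-sided alpha 0.05, no clustering, and a control rate p0 of 20% to 60%. With p1 = p0 + d, p̄ the mean of the two and n = 100:

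power = Φ{ [d − 1.96·√(2p̄(1−p̄)/n)] / √[(p0(1−p0) + p1(1−p1))/n] }

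Solving for 82% gives d of 18.4 to 20.2 points. Now suppose the panel result adds nothing and the advice alone shifts targeted treatment by d. For p0 = 0.40 and d = 0.10: [0.10 − 1.96 × 0.0704] / 0.0700 = −0.54, and Φ(−0.54) = 0.294. Over the range of control rates:

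| Assumed shift from advice alone | Chance of a significant result |
|---|---|
| 5 points | 10.5% to 13.2% |
| 10 points | 29.4% to 37.1% |
| 15 points | 56.6% to 66.3% |
| 20 points | 81.2% to 87.6% |

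The table shows only that a significant result would not by itself imply a contribution from the panel. It is not evidence that the advice has any of these effects.

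**The case against.** The strongest reply is that this is a legitimate trial of a package. The POC-PCR section names the combined arm openly, and testing a diagnostic together with its interpretation is a reasonable pragmatic choice. Objective 7 is a one-line summary. All of this stands, and it limits the point to what the result may be called.

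Second, the call is also how the result is delivered. Results are saved in a microbiological database, and the microbiologist's contact is the only route the protocol describes for getting them to the prescriber at the four-hour plan. That stands too: the call is not a cleanly separable extra. A reader might want to divide the observed difference into a percentage due to the call and a percentage due to the panel. The documents give no basis for any such split. Even so, the discussion covers more than the PCR result, so it is not mere delivery.

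Third, the amendment may have dropped the advice, rather than merely abbreviated the intervention. It does not say so, and the POC-PCR section already has the two-arm design and keeps the advice, so shorthand is likelier. The ambiguity is real, and it has to be resolved whichever reading is right. The amendment's treatment algorithm is in an appendix that is not shown.

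The point cannot be left to the SAP. The objective and the definition of the intervention belong to the protocol, and no analysis can undo the overlap of advice and arm.

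**Conclusion.** The concern holds as a mismatch between the intervention that is randomised and the claim that is stated. The comparison validly estimates POC-PCR plus microbiologist advice against routine microbiology without study-initiated advice. It cannot support a statement about POC-PCR alone.

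This assumes that the advice described in the Procedure and POC-PCR sections is still part of the intervention. The contribution of the advice is unknown and cannot be recovered from this design. The power illustration rests wholly on assumed rates and carries no weight in the conclusion.

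Two stronger readings are tempting and should not be drawn. One is that the randomised comparison is invalid: it is not, once it is named correctly. The other is that the model will be used in departments that have the panel but not the microbiologist's call. The section Significance of the study says only that the model is to be tested in at least eight EDs, and nothing about which components they would have.

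**What to change.** 1. Reconcile the amendment in the outcome section with the Procedure and POC-PCR sections on whether the microbiologist's advice is part of the intervention. In the same edit, remove or explain the mention of three groups.
2. If the advice is part of it, restate objective 7, the heading of the outcome section, the amended intervention and the planned conclusion as *POC-PCR plus microbiologist advice versus routine microbiology without study-initiated advice*. Make no claim for POC-PCR alone, including when the result is carried into the diagnostic model. If the advice was removed, correct the Procedure and POC-PCR sections and state how the result reaches the prescriber.
3. Optionally, have the study microbiologist record a recommendation before seeing the PCR result and again after. Report the share of recommendations that change, as description only. It measures change in the microbiologist's advice, not in the physician's prescription. The recorder is unblinded and may anchor on the first answer, so it does not estimate the panel's own effect on prescribing.

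Items 1 and 2 cost wording only, and the downside is a narrower claim. Item 3 needs no extra arm, sample or patient, but the microbiologist must have the clinical information in hand and commit to a recommendation before seeing the result. The protocol gives no figure from which to cost that time.

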### ***Additional imaging if suspected pneumonia***

Bedside US of the lung will be a FLUS (Focused Lung UltraSound), which examines exclusively for life-threatening conditions. FLUS is used to diagnose pneumothorax, pleural effusion and interstitial syndrome. Video clips will be stored during the scan.

ULDCT of thorax will be performed by a radiologist. The patient will be in horizontal rest. The first 10 participants on each site will enter a pilot study to ensure the best possible image quality of ULDCT via customization of the CT, which are different at each hospital. This to ensure uniform quality and dose. A specially designed technical ULDCT protocol has been developed using a breast phantom (N1 'Lungman', Kyoto Kagaku, Japan) equivalent to an 80 kg man. To develop the protocol a GE Revolution CT (GE Healthcare, Waukesha, IL, USA) with 350 mm scan area and 128x0.625mm detector has been used. The ULDCT will be performed with a fixed tube and without a planning image.

As reference standard a High Resolution Computed Thermography HRCT scan of thorax will be taken at the same time as ULDCT on the same scanner. HRCT will be performed according to standard clinical protocols at each hospital, but only doing inspiration to limit radiation.

The three scans will take place within 24 hours after study recruitment. The results of bedside US, ULDCT, and HRCT will be available to the treating physician, when described. If a result requires immediate action, the clinician will be contacted directly by the examiner. If the participant is discharges from the hospital before the scans have been performed, the scan are offered on an outpatient basis.

### ***Additional imaging if suspected pyelonephritis***

Bedside US of the kidneys will be performed in order to assess whether hydronephrose is present or not. Video clips will be stored during the scan.

An advanced US will be performed at the Radiology Department, and includes Doppler with spectral assessment and registration of RI and PI values in upper, middle, and lower parts of kidneys. It also includes a CEUS (contrast enhanced US) with intravenous injection of 1.5 mL ultrasound contrast. The advanced US will be performed in order to identify inflammatory changes in the kidneys. Video clips from the advanced US will be stored in the Picture Archiving and Communication System (PACS). Clips from CEUS will furthermore be exported anonymously to an external software application (Vuebox) for post-process evaluation.

As reference standard a MRI of the kidneys will be performed at the Radiology Department at the same time (as close as possible) as the advanced US. The scan will include following sequences: planning, Dixon, T1 mapping, T2, T2 mapping, diffusion ADC (100, 400, 800), MRA (3D VIBE angio), and Phase Contrast.

The three scans will take place within 24 hours after study recruitment. The physician responsible for the treatment of the patient, will be informed of the results of the US scans and if MRI, when described. If a result requires immediate action, the clinician will be contacted directly by the examiner. If the participant is discharged from the hospital before the scans have been performed, the scan are offered on an outpatient basis.

### Research biobank

In this study, blood will be collected for a research biobank to store blood until analysis is feasible. Analysis will take place after all samples have been collected.

Biobank blood includes one tube of 10 mL EDTA plasma (suPAR and SP-D) and one tube of 4 mL LiHeparin (YKL-40 and KL-6). All samples will be stored locally in a -80 °C freezer. The samples are pseudonymized with a code to protect the identity of the participants. All samples and code lists are stored safely and separately to prevent unauthorized access.

The expiry date of the research biobank is the last day of recruitment, which is expected to be September 2021. After expiry date, the remaining material in the research bank will be destroyed.

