#### **Serum soluble urokinase plasminogen activator receptor (suPAR)**

Serum suPAR is measured using suPARnostic Tubilatex assay reagents (validated on Cobas c111) protocol for Cobas c702 and c502 applying the Multi-Pack cassettes (Roche Diagnostics, Mannheim, Germany) (42). Calibration is performed at least once a month or in connection to a new batch of TurbiLatex reagents, after calibration a quality control is performed. Serum suPAR is tested within two hours from the collection of the blood sample.

Measure range of the suPARnostic Tubilatex assay is 1.8 µg/L to 16.0 µg/L on Cobas c502 analyzer. The assay's limit of blank, limit of detection and limit of quantification are 1.0 µg/L, 1.2 µg/L and 1.2 µg/L respectively. Expected values for patients attending ED's range from 3-6 µg/L and can reach double digits in patients with severe disease related to poor prognosis. High concentration of SuPAR above 20 µg/L may be false positive results related with interference used by high concentration of hemoglobin, lipids or bilirubin. There is no identified interference in concentrations of bilirubin >350 µmol/L, triglycerides > 3.3g/L, hemoglobin > 1.4 g/L or rheumatoid factor > 440 IU/mL. The highest concentration of suPAR is tested at 47.5 µg/L without hook-effect and the linearity is from 1.8 µg/L to 26.6 µg/L. The mean value of precision of the test is 3.4 µg/L, 7.1 µg/L, 10.2 µg/L for low, middle and high concentrations of SuPAR respectively. The accuracy of suPARnostic Tubilatex is compared with suPARnostic ELISA with similar results < 15 % of difference.

The precision of suPAR assay is expected to be < 5% CV or similar. This is estimated from external quality assessment material, HK 19 (Product code 2226 DK, Lot. No. 201808) analyzed repeatedly during five different days on c502 and c702 and the mean content of suPAR determined by turbidimetry was 2.15 mg/ L and 2.03 mg/L (CV% 4.56 and 5.52) for the Cobas c502 and c702 instruments, respectively.

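### The biobank expires on the last day of recruitment, yet its samples may be assayed only after all have been collected, which puts objective 3 (SP-D, YKL-40, KL-6) at risk

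*Protocol*

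**What the plan says.** The Research biobank section gives the bank's purpose: "blood will be collected for a research biobank to store blood until analysis is feasible". It then sets three rules.

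- Start of analysis: "Analysis will take place after all samples have been collected".
- Expiry: "The expiry date of the research biobank is the last day of recruitment, which is expected to be September 2021".
- Fate of the samples: "After expiry date, the remaining material in the research bank will be destroyed".

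The section lists the analytes as SP-D and suPAR from an EDTA plasma tube, and YKL-40 and KL-6 from a lithium-heparin tube. Storage is local at -80 °C.

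Objective 3, under Hypothesis, aim and objectives, asks: "What is the diagnostic value of the lung injury markers SP-D, YKL-40, and KL-6 on diagnosing pneumonia".

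For suPAR there is a second description. The section on additional infection markers sends EDTA blood to the local laboratory, and the suPAR subsection says: "Serum suPAR is tested within two hours from the collection of the blood sample".

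**The concern.** A biobank that holds samples for one batch analysis has to outlive the end of collection by at least the time the assays take. Here the expiry date coincides with the end of collection. A site could follow the text by clearing the freezer once recruitment closes. It could also keep the tubes for assay and so hold them past the bank's own expiry date.

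What is at stake is objective 3. Its three markers are described only as biobank analytes. Blood drawn at an acute admission cannot be collected again, so destruction before assay could not be undone.

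The suPAR point is smaller and separate. suPAR is one of the three markers in the ROC comparison under Diagnostic value of infection markers, and the protocol describes two ways of handling it without saying which result is used.

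**Working it through.** No sample size or power figure is involved. The check is one of order in time.

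**Inputs**

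- L = last day of recruitment (end of September 2021 is expected, Setting section).
- S = day on which the last sample is collected. Blood is ordered as soon as possible after recruitment and sampling belongs to the steps to be finished within four hours of arrival (Procedure). The last participant's blood is therefore drawn on or about L, and collection cannot be known to be complete before recruitment closes.
- A = earliest permitted start of biobank analysis. By the first rule, A is not before S.
- E = expiry. By the second rule, E = L.
- D = destruction. By the third rule, D comes after E, with no deadline.

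**Time available before expiry**

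E − A ≤ L − S = L − L = 0 days.

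The result does not depend on the calendar date. The Setting section lets enrolment run until the sample size is reached, so L may move. E is defined as L and moves with it, and the gap stays at 0.

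**Order of A and D**

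Analysis and destruction both come after the last sample, and no sentence ranks them. Two readings are possible:

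| Reading of the remaining material | Order | Consequence for objective 3 |
|---|---|---|
| Everything still stored at expiry | Destruction may come before assay | Nothing has been assayed by then, so SP-D, YKL-40 and KL-6 could be lost for every participant with biobank tubes |
| What is left over after assay | Assay comes before destruction | Results exist, but all assays are run on or after the expiry date, and no storage period is stated to cover them |

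**Size**

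The section does not say how many participants contribute biobank tubes. If all do (an assumption), it would be the planned total of at least 1000, of whom at least 250 are expected to have pneumonia. If only patients with suspected pneumonia do, the number is smaller and is not given.

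**suPAR, side by side**

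- Infection marker and suPAR subsections: blood goes to the local laboratory and is tested within two hours.
- Research biobank: "Biobank blood includes one tube of 10 mL EDTA plasma (suPAR and SP-D", with analysis after all collection is complete.
- Diagnostic value of infection markers: PCT, CRP and suPAR are compared by ROC curves, and the suPAR measurement to be used is not named.

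The first two cannot both describe a single suPAR measurement. They could describe two, but the protocol does not say so.

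**The case against.** The best defence is that the paragraph should be read for its purpose. It opens by saying that the bank exists to keep blood until it can be analysed, and the word remaining most naturally means what is left afterwards. Destruction comes after expiry rather than on that day, and no deadline is given. Nobody running this study would discard unassayed tubes. Objective 3 is one of eight, and no stated sample size rests on these markers.

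Much of this stands. A reader might infer that the samples are destroyed on the last day of recruitment and that objective 3 will have no data. The text does not support that inference: it gives no destruction date, and total loss follows only on the strict reading.

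The defence does not remove the conflict. Even when read for its purpose, the paragraph puts every biobank assay on or after the bank's own expiry. No other section sets a storage period beyond that date or states that assay precedes destruction.

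On suPAR, a reader might infer that some participants are tested fresh and others frozen, so that handling confounds the comparison with PCT and CRP. Nothing in the protocol indicates mixed handling, and the biobank entry may be a stored duplicate. Nor does suPAR share the risk to objective 3, because it has the two-hour route. What stands is the unexplained double description.

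**Conclusion.** The expiry rule is wrong as written. It leaves 0 days before expiry for analyses that may begin only once collection is complete, and the order of assay and destruction is not fixed. This puts objective 3 at risk, because the biobank is the only route the protocol gives for its three markers. The possible loss ranges from none (remaining material means leftovers after assay) to all SP-D, YKL-40 and KL-6 results (everything in store at expiry is destroyed first).

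The conclusion rests on the plain wording of the Research biobank section and on blood being drawn at enrolment. It does not depend on the recruitment rate. Whether the approval applied for, mentioned under Ethical considerations and risks, carries the same expiry date cannot be judged, since the application is not available.

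The two suPAR descriptions conflict and need reconciling. No finding of bias in the marker comparison follows from them.

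**What to change.** 1. In the Research biobank section, define expiry and destruction as following completion of all planned biobank analyses, with a stated latest date counted from enrolment of the last patient. State that only material left after those analyses is destroyed.
2. Check that the biobank approval applied for covers that period, and extend it if it does not.
3. Reconcile the suPAR subsection with the Research biobank section. Name the single suPAR measurement that enters the ROC comparison for all participants. If the frozen sample is a reserve or is meant for another purpose, say so. Align the specimen name at the same time, since the suPAR subsection speaks of serum while the tubes are EDTA.

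The cost is a few sentences in the protocol and possibly an amended approval. No extra patients, samples or procedures are needed. The first two changes should be in place before recruitment closes, because destroyed samples cannot be replaced.
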